### Outcomes

The primary outcome is the prevalence of pneumonia complicating stroke within 1 week after baseline. The secondary outcomes include the following: (1) the prevalence of pneumonia complicating stroke within 1, 3, and 6 months after baseline; (2) metagenomic outcomes in terms of composition and relative abundance of oral microbiome in oral rinse samples in 3, 5, and 7 days, and 1, 3, and 6 months after baseline; (3) oral hygiene status and gingival bleeding in 1, 3, and 6 months after baseline; and (4) generic health-/oral health-related quality of life in 1, 3, and 6 months after baseline. The time point for assessing each outcome is illustrated in Fig. 1.

**Fig. 1 Fig1:**
[figure not shown]
The schedule of enrolment, interventions, and assessments

#### Assessment of pneumonia complicating stroke

We will employ the diagnostic criteria of pneumonia complicating stroke developed by the Stroke Consensus Group [21]. The recommended diagnostic criteria for definite and probable stroke-associated pneumonia in patients not receiving mechanical ventilation are as follows. Patient who is diagnosed as definitive case should meet at least 1 of the following: (1) fever (> 38 °C) with no other recognized cause, (2) leukopenia (< 4000 WBC/mm^3^) or leukocytosis (> 12,000 WBC/mm^3^), and (3) for adults ≥ 70 years old, altered mental status with no other recognized cause. And patient should also meet at least 2 of the following: (1) new onset of purulent sputum, change in character of sputum over a 24-h period, increased respiratory secretions, or increased suctioning requirements; (2) new onset or worsening cough, dyspnea, or tachypnea (respiratory rate > 25/min); (3) rales, crackles, or bronchial breath sounds, and (4) worsening gas exchange. Patient should also have no less than 2 serial chest radiographs (CXR) with at least 1 showing new or progressive and persistent infiltrate, consolidation, or cavitation. Probable case also needs to meet all the criteria except that diagnostic changes on the initial CXR and repeat CXR (or where CXR not undertaken) are absent, and no alternative explanation or diagnosis exists. Since most patients are hospitalized within 1 week in this study, it would be feasible for us to diagnose any pneumonia occurring in this period, but it would be challenging to diagnose whether they develop any pneumonia after hospital discharge. We will inquire their medical history and use their medical notes to make diagnosis at their follow-up visits after discharge.

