**Methods/design:**

This study is a randomized, single-blind, parallel trial of 6 months duration. The study is being conducted at one of the largest medical teaching hospitals in Hefei, China. A total of 166 patients with stroke and free from any post-stroke complication will be recruited. After enrollment, patients will be randomized to one of the following groups: (1) oral hygiene instruction (OHI) or (2) OHI, 6-month use of powered tooth brushing, and 0.2% chlorhexidine gluconate mouth rinse (10 ml twice daily). The primary outcome is the prevalence of pneumonia complicating stroke. Patients will be monitored closely for any occurrence of pneumonia over the entire period of this trial. Oral rinse samples will be collected at baseline and multiple follow-up reviews (3, 5, 7 days, and 1, 3, 6 months after baseline). Next-generation sequencing will be employed to detect composition and relative abundances of the microorganism in the oral rinse samples. Questionnaire interviews and clinical oral examinations will be conducted at baseline and 1, 3, and 6 months after baseline.

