## Method

### Participants

This study is a randomized, single-blind, parallel-group controlled trial of 6 months duration. Follow-up reviews will be conducted in 3, 5, and 7 days, and 1, 3, and 6 months after enrollment. Multiple calls will be made 1 week before each follow-up visit to remind participants of their visit. The study was approved by the Biomedical Ethics Committee of Anhui Medical University (reference number: 20170095, see additional file 1) and registered at the ClinicalTrials.gov provided by the US National Library of Medicine (Registration No.: NCT04095780). The protocol was written according to the SPIRIT Checklist (Standard Protocol Items: Recommendations for Interventional Trials, see additional file 2).

The study is being conducted at The Second People’s Hospital of Hefei, Hefei Hospital Affiliated to Anhui Medical University, Hefei, China. This hospital is one of the largest general hospitals in Hefei, which is the capital city of Anhui province. Patients with stroke in acute phase receive care at the Inpatient Stroke Unit, Department of Neurology, and will form the study subjects for this trial. During their inpatient stay in the Stroke Unit, they receive multidisciplinary treatments and support involving physiotherapy, occupational and speech therapy, and social work service. The length of hospitalization is usually 1 week. After discharge, patients with stroke are scheduled for regular follow-ups and outpatient rehabilitation. Our oral health research team is collaborating with the Stroke Unit in helping with oral care for those patients following stroke.

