The following selection criteria are applied: (1) having onset of stroke within 3 days and free of any post-stroke complication; (2) having moderate to severe functional disability—Barthel Index (BI) scores of < 70; (3) being conscious and respiring voluntarily without ventilator; (4) not having any lung disease and lower respiratory infection; (5) not having indwelling naso-gastric feeding tubes; (6) having dysphagia as shown by Gugging Swallowing Screen (GUSS) test; (7) having normal cognitive ability or mild impairment—Mini-Mental State Examination (MMSE) > 18; (7) having the ability to follow instructions (as an assessment of compliance of oral health intervention); (8) not having systemic administration of antibiotics; and (9) not being edentulous. Patients who meet the above selection criteria will be provided with detailed information regarding potential benefits and adverse effects of the interventions, the procedures of this trial, and the anticipated outcomes. They will be asked by a researcher in our team to sign on a written informed consent before enrolling in this study (written informed consent, additional file 3).

According previous studies [12, 13], pneumonia complicating stroke usually occurs within 1 week after stroke. We set the prevalence of pneumonia within 1 week after onset of stroke as the primary outcome of this study since we would like to explore whether oral health promotion interventions could possibly reduce the prevalence of pneumonia after stroke. According to previous epidemiological studies, the prevalence of pneumonia complicating stroke is 20 to 60% [12, 13]. Thus, we hypothesize that in the comparison group, the prevalence of pneumonia complicating stroke within 1 week is 40%, while the prevalence could be decreased to the lower limit of 20% in the interventional group. We set the statistical power at 80% and the statistical significance level at 0.05. Anticipating a 10% dropout rate over the first week of this clinical trial, the initial sample size for each group is proposed as 83 patients per group (166 subjects in total, Gpower 3.0.10 statistical software).

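### Pneumonia at 1, 3 and 6 months: diagnosis after discharge is tied to follow-up visits, with no stated route for patients who stop attending, although pre-visit calls are already planned

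*Protocol article*

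**What the plan says.** The abstract of the protocol article (Methods/design) undertakes that "Patients will be monitored closely for any occurrence of pneumonia over the entire period of this trial". The section Assessment of pneumonia complicating stroke separates two periods. In the first week most patients are in hospital and diagnosis is called feasible. After that, "it would be challenging to diagnose whether they develop any pneumonia after hospital discharge", and the method chosen is: "We will inquire their medical history and use their medical notes to make diagnosis at their follow-up visits after discharge".

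The section Outcomes makes week 1 the primary time point: "The primary outcome is the prevalence of pneumonia complicating stroke within 1 week after baseline". The first secondary outcome is "the prevalence of pneumonia complicating stroke within 1, 3, and 6 months after baseline", which is cumulative from baseline.

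The section Participants adds three relevant facts. On length of stay: "The length of hospitalization is usually 1 week". On the patients: a selection criterion is "having moderate to severe functional disability" (Barthel Index below 70), together with dysphagia. On contact: "Multiple calls will be made 1 week before each follow-up visit to remind participants of their visit". A reminder is the only purpose given for these calls.

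Under Data management, bivariate comparisons are per protocol, and regression analyses fill missing follow-up outcomes by last observation carried forward (LOCF).

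**The concern.** The visits at 1, 3 and 6 months fall after the usual discharge, so the secondary pneumonia outcome depends on patients coming back. These patients are disabled and have dysphagia. One who is readmitted with pneumonia, too ill to travel or dead is among the least likely to attend. The event being counted can thus remove the patient from the count.

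The planned analysis does not repair this. For a patient last seen without pneumonia, LOCF records no pneumonia from then on. A per-protocol comparison may drop the patient altogether. At stake is a cumulative frequency that is too low, and possibly a distorted comparison if attendance differs between arms. The trial already plans to telephone participants before visits, so much of the missing information could be collected at little cost.

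**Working it through.** **No stated figure to reproduce.** The article anticipates 10% dropout in the first week and gives nothing for attendance from 1 to 6 months. The sample size of 83 per group does not bear on this point.

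**Inputs from the article.** Planned week-1 pneumonia is 40% (comparison) and 20% (interventional), with 1:1 allocation. Mean: (0.40 + 0.20)/2 = 0.30.

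**Assumed inputs (not in the documents).**
- m, the share of patients who permanently stop attending after discharge: 10%, 20% or 30%.
- a, the share of attenders with a first pneumonia after week 1: 5%.
- n, the same share in permanent non-attenders: 10%, 15% or 25%.
- The week-1 rate is taken as fully observed and equal in attenders and non-attenders.

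**Formula.** The outcome is cumulative from baseline, so the denominator holds all events up to the time point:

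share unascertained = m·n / (0.30 + (1 − m)·a + m·n)

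| n | m = 10% | m = 20% | m = 30% |
|---|---|---|---|
| 10% | 0.010/0.355 = 3% | 0.020/0.360 = 6% | 0.030/0.365 = 8% |
| 15% | 0.015/0.360 = 4% | 0.030/0.370 = 8% | 0.045/0.380 = 12% |
| 25% | 0.025/0.370 = 7% | 0.050/0.390 = 13% | 0.075/0.410 = 18% |

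**In patients.** The numerator m·n runs from 0.010 to 0.075. With 166 randomised, that is 166 × 0.010 = 1.7 to 166 × 0.075 = 12.5 patients in both arms together. If they are carried forward as event-free, the reported cumulative frequency is 1.0 to 7.5 percentage points too low.

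**Between arms.** With the same m and n in both arms, carrying forward subtracts the same amount from each, and the absolute risk difference is unchanged. If m is 30% in one arm and 10% in the other, with n = 15%, the difference shifts by 0.045 − 0.015 = 0.03. The direction depends on which arm attends less.

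**What the calls could cover.** A call a week before the 1-, 3- and 6-month visits falls at about 3, 12 and 25 weeks. For patients reached, about the last week of each window would remain unknown. For the 3- and 5-day reviews a call a week earlier would precede enrolment, and for the 7-day review it would fall on it. The calls therefore work only for the three later visits, which are the ones at issue.

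**The case against.** **Only attended visits is an inference.** The article names medical notes as a source, and notes can be read without the patient. It also mentions regular follow-up and outpatient rehabilitation. Tracing of missed visits could stand in a fuller protocol. This stands in part: nothing excludes another route. But the article does fix a method, places the use of notes at the visits and calls the task difficult. That is a stated design choice, not merely omitted detail.

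**Missed visits are not lost events.** History and notes look backwards, so a pneumonia before a missed 1-month visit can be found at 3 or 6 months. This stands. Only events after a patient's last attended visit are lost, and the table gives upper values where patients return.

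**Stronger readings that a reader might infer.**
- *A quarter to a half of the pneumonias are lost.* With n = 15%, events after week 1 alone give 0.015/0.060 = 25%, 0.030/0.070 = 43% and 0.045/0.080 = 56%. The arithmetic is right but the denominator is not the one that Outcomes defines. The article also says that pneumonia after stroke usually occurs within 1 week, when most patients are in hospital.
- *The trial's main comparison or its power is undermined.* That would treat the planned 40% and 20% as events that can be missed after discharge. They are week-1 rates. For some patients the last days before day 7 may follow discharge, but a review is scheduled on that day.
- *The results are biased in a known direction.* Only the interventional arm collects replacement products at visits, but the comparison arm is promised the same products at the end of the trial. Neither the size nor the direction of a difference in attendance can be read from the article.

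**Calls do not solve everything.** Some patients and caregivers will not answer. The rule excluding participants with more than 1 week of systemic antibiotics, and the per-protocol analysis, could still remove a pneumonia found by telephone. Both points stand.

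**Conclusion.** The point holds for the secondary outcome of pneumonia within 1, 3 and 6 months. As written, the plan states no way to learn of a pneumonia in a patient who stops attending. This falls short of the abstract's undertaking, and LOCF would turn the gap into a record of no pneumonia.

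The likely size is modest: about 3% to 18% of cumulative events under the assumed range, and 4% to 12% at the middle assumption of 15% later risk in non-attenders. These figures rest on assumed attendance and later risks, on permanent non-attendance, and on a fully observed week 1. The primary outcome is little affected. The change is worth making because it is cheap and collects the outcome, where a missing-data rule can only guess it.

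**What to change.** In Participants and in Assessment of pneumonia complicating stroke:

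1. Use the calls already planned before the 1-, 3- and 6-month visits to ask the patient or caregiver about pneumonia, hospital admission, antibiotic courses and vital status since last contact. Use the same short script in both arms, with the caller blinded to group where possible.
2. Check every reported event against the medical notes, whether or not the patient attends.
3. Determine post-discharge pneumonia status in all randomised patients from visits, calls and notes together.

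Repeating the call after a missed visit would also cover the last week of the window, at the price of an additional call.

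Cost: a few questions on calls already planned, some work to obtain notes for non-attenders, and a wording change; no extra visit. Telephone reports are less specific than an examination, hence the check against notes. The loss is reduced, not removed, because some patients will not be reached. How the antibiotic exclusion and the per-protocol set treat a pneumonia found this way must be settled separately.

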#### Metagenomic outcome assessment

Patients will be instructed to rinse his/her mouth for 60 s with 10 ml of sterile phosphate-buffered saline (PBS, 0.1 M, pH 7.2) and to spit the rinse into a sterile container. The rinsed samples will be centrifuged for 10 min (1700*g*, 4 °C). The pellet will be re-suspended in 1 ml sterile PBS, from which total genomic DNA will then be extracted. Optimized PCR primers will be utilized for amplifying the targeted region (such as V3–V4) of the bacterial 16S rRNA gene. The 16S rRNA amplicons will be isolated and purified for multiplexing high-throughput DNA sequencing. High-quality reads will be classified into different taxonomic groups based on the Human Oral Microbiome Database with a default confidence threshold. To control the sequencing effort across samples within a study, all microbiome data will be rarefied at an acceptable sequencing depth. The within-sample diversity of microbiomes will be assessed by alpha diversity measures such as the Shannon index. Beta diversity measures the overall microbiome similarity between each pair of samples, generating a distance matrix between all pairs of samples within the study. Principal coordinate analysis (PCoA) based on a distance matrix (such as UniFrac or Bray-Curtis) is commonly used to visualize beta diversity data in an unsupervised manner. To determine differences in the relative abundances, classical statistical methods/tools (e.g., Student’s *t* test, ANOVA) or linear discriminant analysis (LDA) effect size (LEfSe) will be used [22].

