Following stroke, 85% of the patients have limb dysfunction in acute phase, which makes them unable to perform oral self-care [4]. A meta-analysis found that compared to healthy controls, patients with stroke had significantly increased DMFT, plaque index, probing depth, and clinical attachment loss [5]. Another systematic review summarized that following stroke, patients have reduced lip force and tongue pressure against hard palate and uncoordinated masticatory muscle movement, all of which collectively lead to the difficulties of identifying the location of food bolus and propelling it into the esophagus [6]. Food debris is more likely to be accumulated in the oral cavity, giving rise to the growth of opportunistic pathogens (aerobic and facultatively anaerobic Gram-negative bacilli, yeasts, *Staphylococcus aureus*). Among those hospitalized patients with stroke in Hong Kong, aerobic and facultatively anaerobic Gram-negative bacilli (AGNB) was isolated among 72.8% of them [7], and yeast was isolated among 55.4 to 59.3% of them [7, 8]. Among those patients with stroke during the rehabilitation period, the prevalence of AGNB still maintains at the level of 47.9% and yeasts at the level of 50.5% [9]. All the aforementioned reflected a higher prevalence of opportunistic pathogens isolated from patients with stroke than healthy subjects [10]. It has been reported that those opportunistic pathogens are associated with aspiration pneumonia. One study recovered pathogens from the protective bronchoalveolar lavage fluid (PBAL) and compared those pathogens to those isolated from dental plaque by pulsed-field gel electrophoresis (PFGE). A number of *S. aureus* and Gram-negative bacilli isolates in PBAL matched genetically those from the corresponding dental plaque [11]. It is thus posited that the oral cavity can be a reservoir of respiratory pathogens responsible for pneumonia among those people with systemic diseases.

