It has been proved that oral opportunistic pathogens and aspiration pneumonia have a strong association [11], yet the ways to detect oral opportunistic pathogens in the aforementioned studies were limited in conventional culture and PFGE. The traditional culture method uses several selective culture media and is only able to detect those species which can be cultured. Presumptively, the identification of pure isolates of species on the selective culture medium is based on colony morphology and the Gram stain method, which largely depends on personal experience and subjective judgment. PFGE can only target several suspicious species and identify them qualitatively. Unlike those conventional techniques, NGS is able to assess the phylogenic structure, relative abundance, and correlation network of the whole oral microbial community. The high-throughput sequencing of 16S rRNA genes can usually provide taxonomic resolution of the whole microbial community at the genus or even species level. In this trial, we will employ the change of composition, relative abundance, and correlation network from metagenomic analysis as part of the outcome measures. Compared to conventional microbiological techniques, the outcomes from the metagenomic analysis are more comprehensive and sensitive to reflect how the whole oral microbial community is affected by the oral health promotion interventions, and how the change of the whole oral microbial community is associated with the risk for pneumonia complicating stroke. In this trial, the oral rinse samples will be collected at baseline and multiple times within 1 week after enrollment. These consecutive samples in a short time interval will provide a close observation of the dynamic change of oral microbial community, and possibly reflect the exact status of the oral microbial community before the event of pneumonia if any participant develops pneumonia. The findings of this trial will provide much-needed evidence for medical professionals in the field of cardiovascular diseases to advocate or disregard the inclusion of oral health promotion interventions into multidisciplinary stroke treatment.

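### Yeasts are among the protocol's target pathogens, but only bacterial 16S is sequenced, so the microbiome claims should be limited to bacteria and one abundance analysis fixed in advance

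*Protocol article*

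**What the plan says.** **Target.** The Abstract (Background) says the trial evaluates whether oral health promotion reduces pneumonia through its effect on oral opportunistic pathogens. The article's Background section lists these as aerobic and facultatively anaerobic Gram-negative bacilli, yeasts and *Staphylococcus aureus*. It reports yeasts in 55.4 to 59.3% of hospitalised patients with stroke and in 50.5% during rehabilitation.

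**Assay.** Under Metagenomic outcome assessment, the primers amplify a region (V3–V4 is the example) "of the bacterial 16S rRNA gene". No fungal marker or culture is described.

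**Claim.** The Discussion states that "NGS is able to assess the phylogenic structure, relative abundance, and correlation network of the whole oral microbial community".

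**Analysis.** The same metagenomic section says: "To determine differences in the relative abundances, classical statistical methods/tools". It then gives Student's t test and ANOVA as examples, or LEfSe as an alternative. Alpha diversity, beta diversity and principal coordinate analysis are also planned. Data management describes between-group tests at baseline and at the follow-up reviews, with rank tests for non-normal outcomes, paired tests within a group over time, and regression for confounders. Outcomes lists the microbiome as a secondary outcome, sampled at days 3, 5 and 7 and at months 1, 3 and 6.

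**The concern.** Yeasts are fungi and carry no bacterial 16S gene that these primers would profile. One of the three pathogen groups in the trial's own causal argument is therefore outside the data, while the text promises coverage of the whole community. The Background says that chlorhexidine's effect on oral opportunistic pathogens in clinical use is unclear. A null microbiome result would leave that question untouched for yeasts, yet a reader of the Discussion would think it answered.

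The second issue is how a difference in abundance will be judged. The article allows classical tests or LEfSe without saying which decides. A choice made after the data are seen can change which taxa are reported as altered. Comparing the arms separately at each review also gives up the information in the baseline sample and multiplies the number of comparisons.

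**Working it through.** **1. Pathogens named against pathogens measurable**

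| Group named in the Background | Within bacterial 16S? |
|---|---|
| Gram-negative bacilli | Yes, as far as reads resolve to genus or species |
| *S. aureus* | Yes as *Staphylococcus*; the species only if reads resolve that far |
| Yeasts | No |

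The Discussion itself says resolution is usually to genus or even species, so the first two rows carry that limit. The Discussion also faults culture for finding only organisms that can be cultured. The Background, however, reports yeasts isolated in earlier hospital studies. For this group the new assay sees less than the methods it is meant to improve on. An analysis plan cannot repair this, because it follows from the choice of marker.

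**2. Use of baseline in the between-arm comparison**

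- Student's t, Mann-Whitney and chi-square tests compare the arms at baseline and at each review. Each uses one visit's values.
- Paired t, Wilcoxon signed-rank and McNemar tests use earlier samples, but within one arm.
- Regression addresses confounders. The list under Collection of other confounding factors (demographics, smoking, brushing habit, last dental visit, grip strength, cognition, comorbidities) has no baseline microbiome measure.

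So no stated between-arm analysis of abundance uses the patient's baseline sample.

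**3. What unadjusted testing would produce**

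The article gives no figure for the microbiome outcome, so there is none to reproduce. Inputs:

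- Follow-up visits: 6 (Outcomes).
- Level: 0.05. The article states it only in the sample size paragraph for pneumonia: "We set the statistical power at 80% and the statistical significance level at 0.05". Applying it to each taxon is an assumption.
- Number of taxa: not given. A range is assumed.

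Expected false positives under no effect = 0.05 × taxa × 6.

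| Taxa (assumed) | Tests | Expected false positives |
|---|---|---|
| 10 | 60 | 3 |
| 50 | 300 | 15 |
| 100 | 600 | 30 |
| 200 | 1,200 | 60 |

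These expectations hold even if the tests are correlated. The chance of at least one false positive does depend on correlation. With 10 taxa and independent tests it is 1 − 0.95^60 = 95.4% over six visits, and 1 − 0.95^10 = 40.1% at a single visit. The count covers between-arm tests at follow-up only; within-arm tests would add to it.

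**4. Price of error control**

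Benjamini-Hochberg is never stricter than Bonferroni, so Bonferroni bounds the loss. Assume 75 evaluable patients per arm (83 × 0.9 = 74.7). The standardised difference detectable with 80% power is (z for the two-sided level + 0.842) × √(2/75).

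- Level 0.05: (1.960 + 0.842) × 0.1633 = 0.46
- 10 taxa, 0.05/60: (3.341 + 0.842) × 0.1633 = 0.68
- 100 taxa, 0.05/600: (3.935 + 0.842) × 0.1633 = 0.78

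**The case against.** A reader might infer that the microbiome outcome cannot answer the opportunistic-pathogen question at all. The documents do not support that. Two of the three named groups are bacteria within the assay's scope. The listed outcome is the oral microbiome, not a yeast endpoint, and the 16S level is stated openly in the Abstract, the Background and the methods. What remains is a mismatch between the stated mechanism and claims on one side and a bacteria-only assay on the other.

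A reader might also infer that the plan will test taxa one by one at 0.05 with no error control and so yield dozens of spurious findings. The article does not say this. The t test and ANOVA are examples, LEfSe is an alternative, community-level analyses are planned alongside, and taxon-by-taxon testing is only a natural reading. Handling of multiplicity for a secondary, high-dimensional outcome may sit in an analysis plan or full protocol that is not shown, so silence on it is no fault in itself. The counts above are therefore conditional. The open choice of method and the separate comparisons at each review do stand, because the article states them.

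Nor are baseline and repeated samples ignored altogether: the paired tests use them within each arm. They are missing from the between-arm comparison, which is the one that bears on the intervention.

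**Conclusion.** The point holds in a limited form. The trial cannot answer its pathogen question for yeasts, which its own Background reports in more than half of hospitalised patients with stroke, and the whole-community claim is too broad. This conclusion needs no assumption beyond yeasts not being bacteria.

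The analysis point is secondary. The abundance method is not fixed, and the stated between-arm tests do not use the baseline sample. Its possible size is 3 expected false positives with 10 taxa and 30 with 100, if tests were left unadjusted at 0.05 over six visits, with the taxon count assumed.

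The primary pneumonia comparison is unaffected. The change should be made because the microbial mechanism is in the trial's title and is presented as its main advance, but it does not threaten the trial's main result.

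**What to change.** **Scope.** In the Abstract, Outcomes and Discussion, limit the microbiome aim, outcome and conclusions to bacteria, and keep the second objective in the Background consistent with this. Add a sentence such as: *Microbiome outcomes refer to the bacterial community profiled by 16S rRNA sequencing; yeasts are not assessed.* This costs a narrower claim and no new assay.

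**Analysis.** Under Metagenomic outcome assessment, replace the open choice with one prespecified between-arm analysis of abundance, adjusted for each patient's baseline abundance. Apply Benjamini-Hochberg control at a 5% false discovery rate across all taxa and visits tested, and label LEfSe exploratory. A mixed model on log-ratio abundances is one suitable option, not a requirement; if chosen, it must say how zero counts are handled.

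The cost is that fewer taxa will be declared significant. Under the Bonferroni bound above, the detectable standardised difference rises from 0.46 to at most 0.68 with 10 taxa or 0.78 with 100. Baseline adjustment may recover part of this.
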